## Materials and methods

### Research hypothesis

Individualized care combined with comprehensive rehabilitation and an informational app is superior to standard care combined with an informational app in terms of body composition and physical performance in patients on the waiting list or pre-waiting list for a kidney transplant.

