#### Secondary outcomes

The secondary outcomes include further alterations in body composition, physical performance, frailty, questionnaires on independence and quality of life, blood parameters, and bone density.

For the assessment of body composition, muscle mass and body fat mass (in kilograms) are additionally measured using bioelectrical impedance analysis, along with waist circumference (in centimeters).

To evaluate physical performance, the 6-min walk test (6MWT) [32], sit-to-stand test (STS60) [33], timed up and go test (TUG) [34], one-legged stance test (OLST) [35], and stair climbing test (SCT) will be conducted. The 6MWT assesses cardiopulmonary endurance by having participants walk a 30-m course for 6 min, covering as much distance as possible. If necessary, participants are allowed to take breaks and resume the test [32]. Lower extremity strength and endurance are evaluated with the STS60. The participants are required to stand up and sit down from a chair without armrests as many times as possible within 60 s. The chair must be securely anchored, and participants must cross their arms over their chest [33]. The TUG test assesses functional mobility. The participants stand up from a chair with armrests, walk to a 3-m mark, turn around, walk back, and sit down again [34]. Balance is evaluated with the OLST. The participant must stand unassisted on one leg, and the duration is timed in seconds from when one foot is lifted off the floor until it touches the ground again. Both sides are tested, with a maximum of 1 min per side [35]. The stair climbing test evaluates functional strength, balance, and agility by asking participants to ascend and descend a specified number of steps. The participants climb up and down one flight of stairs (23 steps) as quickly as possible. They may use the handrail if needed, and this is recorded [36].

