Frailty is assessed according to Fried’s criteria, where participants receive a frailty point for each of the following criteria: (1) unintended weight loss in the past year > 4.5 kg, (2) self-reported exhaustion, (3) weakness (low grip strength), (4) slow walking speed, and (5) low physical activity. Participants scoring 1–2 points are considered prefrail, whereas those scoring ≥ 3 points are considered frail. A low handgrip strength is defined as less than 29–32 kg for men and less than 17–21 kg for women, depending on BMI. A slow walking speed is present when it takes more than 6.5–7.7 s, depending on height, to cover a distance of 5 m. Low physical activity is indicated by a weekly energy expenditure of less than 270 kcal for women or 383 kcal for men.

The Freiburg Questionnaire on Physical Activity is used to assess physical activity [37]. Weekly activities are recorded based on their duration and summed accordingly. This tool also allows simultaneous evaluation of adherence to prescribed physical activity. A score of 15 points is required to meet the recommended guidelines.

To assess independence or the need for care, the Barthel Index is used. To evaluate quality of life specifically in dialysis patients, participants will independently complete the Kidney Disease Quality of Life Instrument (KDQOL).

The blood parameters measured in this study include potassium, phosphate, HbA1c, calcium, creatine kinase, albumin, C-reactive protein, ferritin, parathyroid hormone, vitamin D, leukocytes, hemoglobin, and erythrocytes.

Additionally, bone density will be measured at the baseline visit and at the V2 visit via micro-CT. The total, trabecular, and cortical bone mineral densities of the tibia and radius are measured.

In addition to the primary and other secondary endpoints, participants’ status regarding the kidney transplant waiting list will be considered as an additional secondary outcome. Specifically, remaining on the waiting list and successful transplantation will be recorded and analyzed. Participants who are removed from the waiting list will continue to be followed and, whenever possible, will attend follow-up visits so that their data can contribute to the assessment of the intervention’s effectiveness.

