### Statistical analysis and power estimates

Primary and secondary outcomes will be analyzed via appropriate bivariate statistical tests to assess significant differences between the study and control groups with respect to the absolute and/or relative differences between measurements at the baseline and at the final examination, i.e., the “differences in the changes.” To account for multiple time points and control the risk of Type I error due to multiple comparisons, a Bonferroni correction will be applied to the significance level.

A more detailed analysis of changes in target variables will be carried out via mixed-effect models, which will also include interim examinations and thus provide a more precise picture of the course of the measurements. Moreover, competing risk analysis can be used to differentiate between the marginal probabilities of different end states, such as transplantation or death. All analyses may be further extended to include the estimation of interaction effects between treatment and patient characteristics such as age, sex, and frailty. As indicated above, several events may occur that end study participation. Successful transplantation as well as death also terminate participation, thereby producing missing values in the follow-up examinations. In the bivariate analyses, these missing values will therefore be replaced with the last value carried forward, as participation was conducted per protocol. For other sources of missing data such as deliberate withdrawal of participation, we can assume a missing-at-random structure and use multiple imputation and the corresponding combining rules to adjust effect estimates. In addition, all analyses involving protocol non-adherent participants will follow the intention-to-treat (ITT) principle, meaning that participants will be analysed according to the group to which they were originally assigned, regardless of their adherence to the intervention. This approach preserves the benefits of randomisation and avoids bias resulting from deviations from the protocol. The ITT approach will not involve imputation to compensate for non-adherence itself, but may be complemented by sensitivity analyses where appropriate. As an alternative, we plan to use a joint model that directly links the longitudinal model to the underlying time-to-event processes to account for the different dropout reasons [38].

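### For the secondary outcomes, plain Bonferroni should give way to Holm's step-down procedure, which has the same error control and is never less powerful; the gain is modest and depends on a test family the article does not state

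*Protocol article*

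**What the plan says.** The analysis section of the protocol article (Statistical analysis and power estimates) opens with "Primary and secondary outcomes will be analyzed via appropriate bivariate statistical tests", applied to changes from baseline to the final examination. It continues that, because there are several time points and because many comparisons raise the Type I error, "a Bonferroni correction will be applied to the significance level". It does not say which tests form the family, how many there are or what level results. It sets no order among outcomes.

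The Research hypothesis section claims that the intervention is "superior to standard care combined with an informational app in terms of body composition and physical performance". BMI deviation is the only primary outcome. Physical performance and the rest of body composition are secondary, beside frailty, questionnaires, bone density, waiting-list status and a laboratory panel ("The blood parameters measured in this study include potassium, phosphate, HbA1c, calcium, creatine kinase" and eight more). The sample size paragraph treats multiple-test correction as a possible need and adds 20% for it, to reach 168 patients.

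**The concern.** Bonferroni is a single-step method: with m tests, each is held to 0.05/m, however many of the others are clearly positive. Holm's procedure relaxes the threshold after each rejection at no cost in familywise error. The article therefore names a method for which a strictly better one exists, and this does not depend on what an unseen analysis plan says about the family.

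At stake is power for the secondary outcomes, above all physical performance, which is half of the research hypothesis and has no primary outcome. Recruitment closed on 30.06.2025, so more patients cannot recover lost power. The testing rule still can.

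**Working it through.** **1. The plan's own figures.** Difference 1 kg/m², SD 1.8, so d = 1/1.8 = 0.556. A two-sided 5% two-sample t test needs 51.8 → 52 per arm for 80% power and 69.1 → 70 for 90%. Then 2 × 70 × 1.2 = 168, or 84 per arm. The stated figures are reproduced.

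**2. Possible divisors.** The Secondary outcomes section lists:
- 3 further body-composition measures
- 5 performance tests
- frailty (1)
- 3 questionnaires
- 13 blood values
- 6 bone densities (3 types × 2 sites)
- 2 list-status outcomes

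Sum: 3 + 5 + 1 + 3 + 13 + 6 + 2 = 33. The levels that follow are:
- two time points only: 0.05/2 = 0.025
- the 8 body-composition and performance outcomes: 0.05/8 = 0.00625
- all 33 secondary outcomes: 0.05/33 = 0.0015
- the 33 plus the primary: 0.05/34 = 0.00147
- 33 outcomes at both follow-up visits: 0.05/66 = 0.00076

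**3. What the 20% margin could pay for.** At d = 0.556, 90% power needs 81.7 → 82 per arm at 0.025 (82/70 = 1.17) and 131.04 → 132 at 0.05/33. For 80% power, 0.025 needs 63 per arm (63/52 = 1.21). A 20% increase is about the price of two tests, not of 33.

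**4. Why Holm is never worse.** Order the p-values p(1) ≤ … ≤ p(m) and reject in turn while p(i) ≤ 0.05/(m − i + 1). The first threshold is Bonferroni's 0.05/m and every later one is larger, so every Bonferroni rejection is also a Holm rejection. If m₀ null hypotheses are true, a false rejection requires at least one of their p-values to be at or below 0.05/m₀. That has probability at most m₀ × 0.05/m₀ = 0.05 under any dependence.

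**5. Size of the gain.** The article gives no effect sizes for secondary outcomes. Assumed: standardized effects of 0.4 to 0.5, 84 per arm, normal test statistics, and correlations from 0 to 0.6 over the simulations. Average power per affected outcome:

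| Family | Effect | Bonferroni | Holm |
|---|---|---|---|
| 33 outcomes, 8 to 21 affected | 0.5 | 53% | 54–58% |
| 33 outcomes, 8 to 21 affected | 0.4 | 28% | 29–31% |
| 8 outcomes, all affected | 0.5 | 69% | about 81% |
| 8 outcomes, all affected | 0.4 | 44% | about 54% |
| 2 tests, both affected | 0.5 | 84% | 88–89% |
| 2 tests, both affected | 0.4 | 64% | about 70% |

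The exact t test gives slightly lower single-test power at effect 0.5: 51% at 0.05/33, 68% at 0.05/8, 84% at 0.025 and 90% at 0.05. The gain shrinks when fewer outcomes respond. With 4 of 8 affected at 0.5 it is 3 to 4 points (about 69–70% to 73%); with 1 of 2 it is close to nil.

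**6. Method versus family order.** Moving from Bonferroni over 33 to Holm on the 8 hypothesis outcomes first raises their power from 53% to about 80% at effect 0.5. Of this, 53% to 69% comes from shrinking the family to 8, and only the remaining 11 or so points come from Holm within it. The order has a price. With ten other outcomes also affected (effect 0.5, correlation 0.3), a gate that opens only when all 8 are rejected cuts the others' power from 53% to 37%, and to about 0% if only 4 of the 8 are affected.

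**The case against.** The strongest reply is that the harm depends on a divisor that the article never gives. A reader might infer that every secondary outcome will be tested at about 0.0015. The text does not say so. Its first stated reason is multiple time points, and the 20% margin fits two tests far better than 33. At 0.025 an effect of 0.5 keeps 84% power. This stands: 0.0015 is one reading only. It does not settle the matter the other way either, since the bivariate tests use a single contrast (baseline to final examination) and the sentence also names multiple comparisons.

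Second, the family and its order may properly be left to the analysis plan, in a condensed article above all. That also stands, so the missing family is not the point here. The method is different: it is named, and it can be improved under any family.

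Third, a reader might infer that adopting Holm lifts power from 53% to about 80%. It does not. Most of that rise comes from giving eight outcomes priority over the rest, which takes power from quality of life, list status, blood and bone outcomes. Treating all outcomes equally is a valid choice.

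**Conclusion.** The point holds as a modest, near-free improvement. For the secondary outcomes, Holm's procedure gives the same familywise error as the stated Bonferroni correction and at least as much power, without further assumptions. At effects of 0.4 to 0.5 with 84 per arm, the gain is about 1 to 5 points over a family of 33, about 10 to 12 over a family of 8 if all are affected, and about 5 for two tests if both are affected. These sizes rest on assumed effects, correlations and numbers of affected outcomes, and on 84 per arm providing final data. The direction rests on none of them.

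The documents do not support the claim that the trial has fixed a level of about 0.0015. Whether the primary outcome needs correction is a separate question.

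**What to change.** For the secondary outcomes, replace the Bonferroni correction by Holm's step-down procedure in the analysis section and name the family it covers. This costs one or two sentences, no patients and no data. The one practical loss is that Holm has no simultaneous confidence intervals as simple as Bonferroni's, so the article should say which intervals will be reported.

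Optionally, and only before the 12-month comparison by arm is run, make the outcomes of the research hypothesis (body composition and physical performance) the first Holm family at 5%. Report the rest as exploratory with unadjusted confidence intervals. Frailty must then be assigned explicitly: the Abstract lists it under physical performance, while the Secondary outcomes section and Table 1 list it separately, so the family has 8 or 9 members. The plan should state the cost: quality of life, list status, blood and bone outcomes lose confirmatory standing, or lose much of their power if they are kept behind a strict gate.

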### Study design overview

The Smart & Fit for Kidney Transplantation trial is designed as a randomized, controlled, monocentric trial with two parallel groups. Patients and care providers will not be blinded as this is not possible due to the intervention design. The study is being conducted at the University Hospital Erlangen in Germany. Recruitment is carried out via the waiting list for kidney transplantation at the Transplantation Center Erlangen-Nuremberg. Patients in the intervention group will undergo 3 weeks of comprehensive rehabilitation in a nephrology rehabilitation clinic or, if they require care and are of a suitable age, in a geriatric rehabilitation clinic. The intervention group will receive individualized exercise and nutritional support for patients with chronic kidney failure, including an informative app about chronic kidney disease, and the control group will receive only the informative app. The patient allocation ratio is 1:1. The outcome measures will be measured at three time points: (1) directly after signing the confirmation of participation, (2) 6 months later, and (3) 12 months later. To ensure comparability between the three measurement time points, the tests are conducted on the same weekday. This is particularly important with regard to dialysis. The SPIRIT reporting guidelines were followed in the preparation of the manuscript [24].

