#### Intervention group

The participants in the intervention group will receive access to the same app in addition to standard care. In addition to the standard functions, users can connect the app to the university hospital, allowing vital signs and blood parameters to be displayed directly within the hospital’s system. Participants in the intervention group will also complete a 7-day nutrition and activity log. Personalized nutrition and exercise recommendations are provided on the basis of this log, the results of the baseline assessment, and the blood and vital parameters transmitted through the app. Individualized training plans for exercise, consisting of endurance training guidelines and exercises for resistance and balance training, will be provided to patients. The recommendations are based on the WHO guidelines on physical activity, which include: aerobic exercise for at least 150 min per week at moderate intensity, resistance training twice per week, and balance training twice per week [25]. For nutrition, recommendations tailored to the patient’s goals (weight reduction, weight gain, improvement of blood values, etc.) and easily integrable into daily life will be given.

This individualized care aims to counteract the reduction in physical performance and promote the optimization of body composition. In addition, participants in the intervention group will undergo a 3-week inpatient rehabilitation program, during which they will receive intensive care from physicians, physiotherapists, occupational therapists, sports therapists, psychologists, and nutritionists. The rehabilitation takes place between Visit 2 and Visit 3, as sufficient time must be allocated for the application process and participant preparation. The rehabilitation clinic has confirmed in advance that adequate capacity is available to accommodate participants in the intervention group.

Regular telephone check-ins (every 2 months) will be conducted to monitor and potentially adjust the recommendations between visits. During these telephone check-ins, general well-being is assessed, and adherence to or difficulties with the recommendations are discussed. Study participants are informed about these contacts on the day of enrollment. Regular contact is intended to ensure adherence to the implementation of recommendations as well as compliance with scheduled visits.

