### Data collection and outcomes

The data will be collected according to the study timeline displayed in Fig. 1 and described in Table 1. Each visit follows the same protocol and sequence of examinations, ensuring that there is no bias, particularly with regard to blood values and physical performance outcomes. The data will be entered into an electronic database on the same day and verified by a second study staff member. Only the study team has access to the original data. This electronic database does not contain any personalized data; participants are assigned a study ID, which can only be decoded by the study team. The data can only be accessed through a secure login at the University Hospital Erlangen and are protected by a password. The principal investigator grants access to the de-identified data only to individuals involved in the analysis. A participant will be withdrawn if they undergo transplantation, pass away, or withdraw their informed consent.

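### Carrying the last value forward after transplant or death attenuates the 12-month contrast, and no stated estimand makes that value the target

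*Protocol article*

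**What the plan says.** All references are to the protocol article.

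- **Test.** Under Statistical analysis and power estimates, primary and secondary outcomes are compared between groups by bivariate tests "with respect to the absolute and/or relative differences between measurements at the baseline and at the final examination".
- **Transplant and death.** Data collection and outcomes states: "A participant will be withdrawn if they undergo transplantation, pass away, or withdraw their informed consent". The statistical section adds: "Successful transplantation as well as death also terminate participation, thereby producing missing values in the follow-up examinations". Its rule for these values is: "In the bivariate analyses, these missing values will therefore be replaced with the last value carried forward, as participation was conducted per protocol".
- **Other missing data.** For deliberate withdrawal and similar causes, "we can assume a missing-at-random structure and use multiple imputation and the corresponding combining rules to adjust effect estimates".
- **Other models.** Mixed-effects models are described as a more detailed analysis that also uses the interim visit. A competing-risk analysis is mentioned as possible. Then: "As an alternative, we plan to use a joint model that directly links the longitudinal model to the underlying time-to-event processes". None of these is ranked above the bivariate test.
- **Timing.** Study design overview places the assessments at baseline, 6 and 12 months. Under Intervention group: "The rehabilitation takes place between Visit 2 and Visit 3".

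Participants who are removed from the waiting list stay in follow-up (Secondary outcomes), so the carry-forward rule concerns only transplant and death.

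**The concern.** The quantity under test is change from baseline to the final examination. Last observation carried forward (LOCF) answers that question only if the outcome would have stayed where it was last seen. Here the substituted values are of two kinds:

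- **Event before month 6:** only the baseline exists, so the change is set to exactly zero.
- **Event between months 6 and 12:** the 6-month value is used. It was taken before the rehabilitation and so cannot contain any effect of it.

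Both kinds shrink a true 12-month difference. The reason given, participation according to protocol until the event, concerns adherence and says nothing about what the outcome is or would have been at 12 months. A different target, such as the value while still waiting, could justify the last pre-event value, but the article does not state one. A reader of the results would take the figure as a 12-month effect.

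**Working it through.** **Inputs from the protocol article:** difference 1 kg/m², SD 1.8, significance level 5%, 52 or 70 per group for 80% or 90% power, total 168 (84 per arm at 1:1), visits at 0, 6 and 12 months.

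**Assumptions, because the article gives no figures:** event rate e per arm of 5–30% by 12 months; share s = 0.5 of events before month 6; fraction f = 0 to 0.5 of the effect present at month 6; variance of the 6-month change half that of the 12-month change.

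**Step 1. Reproduce the plan's figure.** A two-sided two-sample t test needs 51.8, so 52 per group (80%), and 69.1, so 70 per group (90%). 2 × 70 × 1.2 = 168. The sample size reproduces.

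**Step 2. Expected LOCF difference, equal event rates, true difference 1.**
Difference = 1 − e·s − e·(1 − s)·(1 − f). With s = 0.5 this is 1 − e for f = 0, and 1 − 0.75e for f = 0.5.

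**Step 3. Simulation, 84 per arm, 6,000 runs per setting.**

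| e | LOCF difference | LOCF SE | SE, observed 12-month values only | 95% coverage of the 12-month effect | Power with LOCF |
|---|---|---|---|---|---|
| 5% | 0.95–0.96 | 0.273 | 0.28 | about 95% | 93–94% |
| 10% | 0.90–0.93 | 0.27 | 0.29 | about 94% | 92–93% |
| 20% | 0.80–0.85 | 0.26 | 0.31 | 89–91% | 88–91% |
| 30% | 0.70–0.78 | 0.25 | 0.33 | 78–85% | 81–88% |

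With nobody missing, SE = 1.8 × √(2/84) = 0.277 (0.278 before averaging over runs) and power is about 95%.

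**Step 4. Where the coverage loss comes from.** At e = 20%, the shift divided by the SE is 0.20/0.259 = 0.77 (f = 0) or 0.15/0.258 = 0.58 (f = 0.5). Coverage = Φ(1.96 − shift/SE) − Φ(−1.96 − shift/SE) gives 0.88 and 0.91, against 0.889 and 0.911 simulated. The shift accounts for the loss.

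**Step 5. Standard error.** Without a treatment effect, the LOCF variance is 1.8² × [(1 − e) + e/4]. At e = 20%, SE = 0.277 × √0.85 = 0.256. That is about 8% below the value with complete data (0.256/0.277 = 0.92), so the substituted values count as real information and more.

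**Step 6. No treatment effect (10,000 runs per setting).** With equal event rates, rejection is 4.8–5.0% without drift and 5.0–5.3% with drift. With unequal rates and a common linear drift D, the expected false difference is 0.75 × D × (e₁ − e₀):

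- D = 1, 20% v 10%: 0.075 (simulated 0.073), type I error 5.5%.
- D = 1, 30% v 10%: 0.15, type I error 8.8%.

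**Step 7. Visit labels.** The rehabilitation argument reads Visit 3 as 12 months, the only reading with three assessments that contains a Visit 3. Secondary outcomes, however, labels the second bone-density measurement V2, while the Abstract places it at 12 months, and Table 1 uses 0, t1 and t2. These labels need reconciling.

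**The case against.** **The target may be different.** The primary outcome is about weight optimisation for transplant eligibility, so for a transplanted participant the last value before surgery is arguably the relevant one. Someone transplanted before rehabilitation never received it. This is a fair reading, but the article does not state it. The rule rests on adherence, and the test is defined on the final examination. What stands is that attenuation is measured against the 12-month effect; under a declared while-waiting estimand it would not be called bias.

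**The remedy is already planned.** Mixed and joint models are named, and LOCF is confined to the bivariate tests. That is true and makes the fix cheap. The models are unranked, however, and the bivariate test is described first for the primary outcome.

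**The event rate may be low.** The article cites an average German wait of 8–10 years. Read crudely as a constant rate, that is 1/10 to 1/8, or 10–12.5% a year, and pre-waiting-list patients are also eligible. No death rate is given. At 10% the loss is modest and power at 5% stays above 90%.

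**Stronger readings that a reader might infer:**

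- *That the standard error is wrong by 17% (0.256 v 0.310).* This compares LOCF with a different estimator on fewer patients. The reported LOCF standard error matches the sampling spread of the LOCF statistic, and the fair comparison is 0.277.
- *That false positives are likely.* This needs unequal event rates together with a common drift. The article supports neither, and a drift of 1 kg/m² equals the whole planning effect.
- *That arms must differ in events because changing transplant or death rates is the trial's purpose.* The stated aim is body composition and physical performance; waiting-list status and transplantation are an additional secondary outcome.

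**Conclusion.** The concern holds in a limited form. The article states a carry-forward rule for transplant and death whose reason does not support it, and gives no estimand that would. As a measure of the 12-month contrast, the result is attenuated by roughly 4–5% at a 5% event rate, 8–10% at 10% and 15–20% at 20%. Coverage of the 12-month effect is about 94% at 10% and 89–91% at 20%, mainly because of the shift. These figures rest on the assumed event rate, half of events before month 6, and 0–50% of the effect present at month 6.

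With equal event rates the direction is toward no effect and the 5% level is kept. A false difference needs unequal rates plus drift: 0.15 kg/m² and a type I error of about 9% in the most extreme case examined. This should be fixed, but at plausible low event rates it does not by itself undermine the trial.

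**What to change.** 1. State the estimand for transplant and for death. If the 12-month effect had participants stayed alive and on dialysis is meant, say so. If the value while waiting is meant, say that instead and do not present the result as a 12-month effect.
2. For the 12-month contrast, name one already planned model as primary: the mixed model (arm by visit, baseline deviation, age stratum, all observed visits before the event) or the joint model.
3. Report transplant and death by arm, with the competing-risk analysis already mentioned.
4. Keep LOCF at most as a sensitivity analysis, and delete the adherence argument as its justification.
5. Reconcile the visit labels.

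**Cost:** wording only, with no new data. The confidence interval will be somewhat wider. Using observed 12-month values alone, the standard error would be 0.29 at 10% events and 0.31 at 20%, against 0.27 and 0.26 with LOCF. A mixed model that also uses the 6-month values would be expected to fall below those observed-only figures, though this was not calculated. Recruitment closed on 30.06.2025, so 12-month visits run to about mid-2026; the change should be recorded before outcome data are compared by arm.
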